### Statistical analysis

#### Sample size calculation

The sample size calculation for this study was performed to detect a between-group difference of 1 point in the outcome pain intensity as measured by the Portuguese version of the *Pain Numerical Rating Scale*[25] (with an estimated standard deviation of 1.84 points) and of 4 points in the disability outcome measured by the Roland Morris Disability Questionnaire [26] (with an estimated standard deviation of 4.9 points) with an statistical power of 80%, an alpha of 5%, and a possible loss of follow up of 15%. Given these parameters, 74 patients per group or a total of 148 participants will be necessary.

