**Methods/design:**

One hundred and forty-eight patients will be randomly allocated to a four-week treatment program based upon the *McKenzie *or *Back School *principles. Clinical outcomes (pain intensity, disability, quality of life, and trunk flexion range of motion) will be obtained at follow-up appointments at 1, 3 and 6 months after randomisation. The data will be collected by an assessor who will be blinded to the group allocation.

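### The stated sample size of 74 per group does not follow from the stated inputs, which give about 63 to 65 per group; inputs, power and N need to be made consistent

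*Protocol article*

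**What the plan says.** The Protocol article, under Sample size calculation, gives a full set of inputs and a result.

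- Pain: a "between-group difference of 1 point in the outcome pain intensity", "with an estimated standard deviation of 1.84 points".
- Disability: a difference "of 4 points in the disability outcome measured by the Roland Morris Disability Questionnaire", "with an estimated standard deviation of 4.9 points".
- Error rates and loss: "with an statistical power of 80%, an alpha of 5%, and a possible loss of follow up of 15" per cent.
- Result: "Given these parameters, 74 patients per group or a total of 148 participants will be necessary".

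The Abstract (Methods/design) repeats the total: "One hundred and forty-eight patients will be randomly allocated".

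The Procedures section names pain and disability at 4 weeks as the two primary outcomes. The sample size section does not state whether the test is one- or two-sided. It mentions no division of alpha between the two outcomes, no design effect for the group sessions in the Back School arm, and no inflation other than the 15% loss.

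**The concern.** The text presents 74 per group as the consequence of the listed parameters. That can be checked from the article alone, with nothing left to a fuller protocol or analysis plan. When the parameters are put into the standard formula, the answer is lower by 9 to 11 patients per group. That is too much for rounding or for the choice between a normal and a t calculation.

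What is at stake is the meaning of the main planning figure. If all the stated inputs are right, the trial has more power than it says. If one of them is misreported, a reader does not know which SD, alpha or power the trial was really built on, and cannot judge a borderline or null result for pain against the right benchmark.

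**Working it through.** **Inputs** (all from Sample size calculation): pain difference 1, SD 1.84; disability difference 4, SD 4.9; power 80%; alpha 5%; loss 15%; equal groups (74 + 74 = 148). Assumed: two-sided test, comparison of two means.

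**Formula.** Evaluable patients per group: n = 2 (z₁₋α/₂ + z₁₋β)² (SD/difference)². At two-sided 5% and 80% power, (1.960 + 0.8416)² = 7.849.

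**Attempt to reproduce 74.**

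- Pain: 2 × 7.849 × 1.84² = 53.15, so 54. The t-test calculation gives 54.1, so 55.
- Pain with 15% loss, dividing by 0.85: 53.15/0.85 = 62.5 (63); 54/0.85 = 63.5 (64); 55/0.85 = 64.7 (65).
- Pain with 15% loss, multiplying by 1.15: 54 × 1.15 = 62.1 (63); 55 × 1.15 = 63.3 (64).
- Disability: 2 × 7.849 × (4.9/4)² = 23.6, so 24; t-test 24.6, so 25. With loss, 28 to 30.
- One-sided 5% for pain: 42 to 43 evaluable, 49 to 51 with loss, which is further from 74.
- Both outcomes required to succeed together (treated as independent): 55 evaluable, 55/0.85 = 64.7, so 65.

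No reading of the stated inputs reaches 74. Pain drives the size at 63 to 65 per group, or 126 to 130 in total. The excess is 148 − 130 = 18 to 148 − 126 = 22 patients, which is 18/130 = 14% to 22/126 = 17%.

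**Power at the stated N.** 74 × 0.85 = 62.9, about 63 completers per group. For a two-sample t-test at two-sided 5%, power is 85.7% for 1 point in pain and 99.5% for 4 points in disability. The normal approximation for pain agrees: √(63/2)/1.84 − 1.960 = 1.09, which corresponds to 86.2%.

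**Unstated inputs that come near 74 for pain.** None of these is in the document; they show only that the cause cannot be identified from the result.

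| Change | Calculation | Per group |
|---|---|---|
| SD 2.0 instead of 1.84 | 2 × 7.849 × 4 = 62.8; 62.8/0.85 = 73.9 | 74 (75 if 62.8 is first rounded up to 63) |
| 15% loss applied twice | 53.15/0.85/0.85 = 73.6 | 74 |
| Alpha 2.5% per outcome | 64.36 × 1.15 = 74.01 | 74 if rounded down, 75 if rounded up; the t-test version divided by 0.85 is 66/0.85 = 77.6 (78) |
| Power 85% | 61/0.85 = 71.8; 62/0.85 = 72.9 | 72 to 73 |
| Power 90%, no loss | – | 72 to 73 |

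**The case against.** The strongest reply is that the discrepancy does no harm. The trial is larger than its inputs require, the promised 80% power is met at the stated alpha, and neither the estimate nor the error rate of the primary comparison is affected. This stands, and it limits the finding to a reporting and reproducibility defect.

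A second reply is that the investigators may have allowed for something sensible, such as the two primary outcomes or the Back School group sessions. They may have, but the sentence attributes 74 to the parameters it lists, and neither allowance is among them. If one was made, stating it would resolve the point.

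A third is that the power figures above are for an unadjusted two-sample comparison, while Treatment effectiveness analysis plans linear mixed models. That is a fair limit on the precision of 86%. It does not rescue 74, because the sample size section gives only a difference and an SD for each outcome and no correlation or other model input.

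A reader might go further and infer that the alpha is what is wrong: that 5% was silently split into 2.5% for each primary outcome, which would leave about 78% power for pain with 63 completers. The document does not support that inference. It mentions no split, the match to 74 depends on rounding 74.01 down, and an SD of 2.0 or a doubled loss allowance fits at least as well. The 78% is an illustration of what would follow if a split had been used, not a property of the plan.

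**Conclusion.** The stated inputs, power and N are mutually inconsistent. On the stated inputs, with a two-sided test assumed, pain requires 54 to 55 evaluable and about 63 to 65 randomised per group, against 74 stated; disability requires 28 to 30. A one-sided test would widen the gap, so the conclusion does not depend on the assumed sidedness.

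The document does not reveal which element is misreported, so it would be wrong to single out alpha, power, the SD or the N. It would also be wrong to read this as an underpowered trial. If the stated SDs, alpha and 15% loss hold, power is about 86% for pain and over 99% for disability by a two-sample t-test.

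**What to change.** Keep 148 and make the statement consistent, after going back to the original calculation.

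- If the stated SDs and a two-sided 5% alpha are right: state that 148 randomised with 15% loss (about 63 per group) gives about 86% power for 1 point in pain and over 99% for 4 points on the Roland Morris questionnaire, by a two-sample t-test.
- If another input was used, for example a different SD, an alpha divided between the two primary outcomes, or a further inflation: state that input and the power that follows from it.

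In either case, state the sidedness, say that pain determines the size, and say how the 15% loss was applied. The cost is one or two sentences; enrolment does not change.

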#### Treatment effectiveness analysis

All of the statistical procedures will be conducted on a intention-to-treat basis [28]. In our primary analysis, we will use linear mixed models model to test for the effect of treatment on outcomes at 1, 3 and 6 months follow-up. A treatment effect size will be calculated for each of the follow-up time points and, if there is a statistically significant treatment effect at any time point. The software packages *SPSS 19 *and *SigmaPlot 10 *will be used for this analysis.

## Discussion

In this study, we present the rationale and design for a randomised controlled trial comparing the effects of the *McKenzie *and *Back School *methods in patients with chronic low back pain. The results of this study will be published once the study is concluded.
